### Sensitivity analysis

Although unlikely, it is conceivable that surgeons beginning to operate under an unfamiliar anaesthetic regime (more likely local than general) may have more operative problems than usual. We will be discussing how to analyse the trial without the 'learning curve' with colleagues and the Data Monitoring Committee.

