### Data analysis

Data analysis will be performed by the Principal Investigators in collaboration with the trial statistician at the Neurosciences Trials Unit, Edinburgh University. Trial data will be presented according to the CONSORT guidelines [5]. All analyses unless otherwise stated will be by intention-to-treat and will compare all patients allocated to general anaesthesia with all those allocated to local anaesthesia. For the primary outcome, we will present the relative and absolute differences in the proportion of patients alive and stroke-free (including retinal infarction) and without myocardial infarction at 30 days after surgery, or 30 days after randomisation for those few patients for whom surgery was scheduled but was never carried out. A variety of other secondary analyses (with due allowance for their exploratory nature) will be performed to compare: survival to 30 days post-surgery, other peri-operative adverse events; survival analysis of stroke, myocardial infarction and death in the longer term at one year; length of stay in recovery, high dependency unit, intensive therapy unit and overall; and health related quality-of-life at about 30 days post-surgery.

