### Organisation

The Steering Committee will usually meet every six months to review the progress of the trial, including the overall complication rates of surgery. However, apart from the trial statistician, all the members of the committee will remain blinded to any outcomes and other important results divided by treatment allocation.

All members of the Data Monitoring Committee will be totally independent of the trial. The Data Monitoring Committee will regularly review the recruitment into the trial, trial discipline, the baseline data and the main outcomes. They will advise the Steering Committee on the adequacy of recruitment, the balance of the two treatment arms, and that there is no accumulating evidence of harm to one arm or the other. In this task they may request whatever unblinded analyses they wish from the trial statistician, and at whatever interval they wish. The Committee may also wish to consider any new information arising from other studies. All unblinded analyses are supplied to the Data Monitoring Committee in confidence.

The Data Monitoring Committee will advise the chairman of the Steering Committee if, in their view, the randomised comparisons have provided both: (i) 'proof beyond reasonable doubt' that for all, or some patients, one method of anaesthesia is clearly indicated or clearly contra-indicated; and (ii) evidence that might reasonably be expected to materially influence future patient management. Appropriate criteria of proof beyond reasonable doubt cannot be specified precisely, but we imagine the DMC will work to the well established guide that a difference of at least 3 standard errors in an interim analysis of the primary outcome events (between patients allocated local anaesthesia and patients allocated general anaesthesia) may be needed to justify halting or modifying the study before the planned completion of recruitment. This criterion has the practical advantage that the exact number of interim analyses is of little importance, and so no fixed schedule is proposed.

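### How to analyse the trial without the learning curve is to be discussed with a committee that may see results by arm, and nothing shields that choice from those results

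*Protocol article*

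**What the plan says.** The Sensitivity analysis section gives the reason for the analysis: "surgeons beginning to operate under an unfamiliar anaesthetic regime (more likely local than general) may have more operative problems than usual". On how it will be done, it says only "We will be discussing how to analyse the trial without the 'learning curve' with colleagues and the Data Monitoring Committee".

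The Organisation section describes what that committee sees. "The Data Monitoring Committee will regularly review the recruitment into the trial, trial discipline, the baseline data and the main outcomes". It adds "In this task they may request whatever unblinded analyses they wish from the trial statistician, and at whatever interval they wish", and then "All unblinded analyses are supplied to the Data Monitoring Committee in confidence".

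The same section protects the Steering Committee: "apart from the trial statistician, all the members of the committee will remain blinded to any outcomes" and other important results by allocation. On the final analysis, the Data analysis section says "Data analysis will be performed by the Principal Investigators in collaboration with the trial statistician".

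The primary comparison is set elsewhere. The Randomisation and Data analysis sections make it intention-to-treat, with every allocated patient counted.

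**The concern.** An analysis that sets aside early experience may leave out randomised patients. Its result depends on choices such as whose experience counts (surgeon, anaesthetist or centre), how many early cases are set aside, and whether both arms are treated alike. These choices are harmless if made without knowledge of the results by arm. If made with that knowledge, they can move the estimate in a wanted direction, even without intent.

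The article keeps almost the whole Steering Committee blinded, yet it names the one committee with free access to unblinded results as a party to designing this analysis. The choice is also not neutral in expectation, because the article thinks the problem likelier under local anaesthesia, the technique it predicts will do better.

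At stake is the credibility of the sensitivity analysis. If local anaesthesia showed no benefit, readers would ask whether inexperience hid one. If it did show a benefit, they would ask whether setting aside early cases changes it. An analysis whose rule may have been informed by the results answers neither question well.

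**Working it through.** **1. The passages side by side**

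| Question | What the article says | Section |
|---|---|---|
| Who is consulted on the learning-curve analysis? | Colleagues and the Data Monitoring Committee | Sensitivity analysis |
| What may that committee see? | Main outcomes regularly; any unblinded analysis, at any interval | Organisation |
| Who else sees results by arm? | The trial statistician, who also takes part in the final analysis | Organisation; Data analysis |
| Is the choice timed before a look by arm, or limited to blinded data? | Not stated | – |

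Confidentiality limits what the committee passes on. It does not stop its advice from being informed by what it knows.

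**2. The plan's own figure**

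Inputs from Sample size: 5,000 patients, 7.5% against 5%, 5% level. Equal arms of 2,500 are read from the balanced blocks; a two-sided test is assumed.

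- Standard error under no difference: √(2 × 0.0625 × 0.9375 / 2,500) = 0.00685
- Standard error under the planned difference: √((0.075 × 0.925 + 0.05 × 0.95) / 2,500) = 0.00684
- z = (0.025 − 1.96 × 0.00685) / 0.00684 = 1.69, so power = 95.5%

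The stated power of more than 90% is reproduced. The concern does not rest on it.

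**3. What a free choice of cut-off could do (illustration)**

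Assumptions: 100 centres (the article says at least 100) of 5,000 / 100 = 50 patients each; no true effect; event rate 6.25% in both arms, the midpoint of 7.5% and 5%. The rule drops the first k patients at each centre from both arms. The article gives no k, so the values are assumed. For each k, with n = (5,000 − 100k) / 2 patients per arm,

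Z = (p̂₁ − p̂₂) / √(2p̄(1 − p̄) / n).

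A false positive is counted when any version on offer has |Z| > 1.96. Results from 100,000 simulated trials:

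| Versions on offer (k) | Chance that at least one is significant |
|---|---|
| 10 only, fixed in advance | 4.9% |
| 5, 10 | 6.5% |
| 5, 10, 15 | 7.9% |
| 5, 10, 15, 20 | 9.2% |
| 5, 10, 15, 20, 25 | 10.7% |

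A repeat with 400,000 trials and a different seed gave 5.0%, 6.5%, 7.9%, 9.3% and 10.7%. The full analysis (k = 0) is left out of every row, so the table describes the sensitivity analysis alone. Each row is a worst case, in which the most extreme version is always reported.

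**4. What a fixed rule costs in precision**

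With one k fixed in advance and the planned 7.5% against 5%, the power formula in step 2 gives:

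| k per centre | Patients left | Power |
|---|---|---|
| 5 | 4,500 | 93.4% |
| 10 | 4,000 | 90.5% |
| 15 | 3,500 | 86.4% |
| 20 | 3,000 | 80.8% |

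The analysis stays informative under a fixed rule, so nothing is gained by leaving the choice open.

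**The case against.** The strongest reply is that the article describes a consultation and nothing more. The Data Monitoring Committee is independent of the trial and holds unblinded results in confidence, and the discussion may take place before any look by arm. The analysis is a sensitivity analysis of a problem the article itself calls unlikely. The Intervention section reduces that problem by expecting at least five local anaesthesia procedures at each centre before it randomises. Details such as the cut-off and the unit can properly be left to a full protocol or analysis plan that is not shown here.

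Most of this stands, and it limits the point. The missing cut-off and unit are not counted as faults. What remains is something the article does state: a committee with access to results by arm is a party to designing the analysis, with no condition on timing or on the data used. An analysis plan that followed this text would carry the weakness forward.

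A reader might infer more than the documents support:

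- **That the committee will decide the rule.** The text speaks of discussion; no section gives the committee that decision.
- **That only early local anaesthesia patients will be dropped.** The remark that the problem is likelier under local anaesthesia explains why a learning curve might exist. It proposes no one-sided exclusion, and dropping cases from both arms or fitting an interaction fits the text equally well.
- **That the trial's false-positive rate doubles.** The primary analysis is fixed as intention-to-treat, and this choice cannot change it.
- **That this analysis would settle how a neutral or adverse result is read.** The article gives it no such role.

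**Conclusion.** The concern holds in a limited form. The article names a committee with unrestricted access to results by arm as a party to designing the learning-curve analysis, and does not require the choice to precede those results or be shielded from them. Whether the choice would in fact be influenced cannot be known from the text; the weakness is the missing safeguard.

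In the illustration, the false-positive rate of this one analysis rises from about 5% with a fixed cut-off to between 6.5% and 10.7% with a free choice among two to five. Those figures rest on equal centres, assumed cut-offs, the same exclusion in both arms and always picking the most extreme result, so they show what is possible and are not a forecast. The primary result and its error rate are unaffected. Severity is moderate: worth correcting, but no threat to the main conclusion.

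**What to change.** In the Sensitivity analysis section, delete the reference to the Data Monitoring Committee and state that:

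- the blinded Steering Committee members will fix the rule in a dated document, without input from the Data Monitoring Committee and without drawing on the unblinded statistician's knowledge of results by arm;
- the rule names the unit of experience (surgeon, anaesthetist or centre) and the number of initial randomised cases to set aside;
- the same exclusion applies to both arms, by allocation, for example alongside a test of treatment by order of randomisation in the full intention-to-treat set;
- the document records whether any look by arm had already taken place;
- the result is labelled as supportive of the intention-to-treat analysis.

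The number of cases is for the blinded members to choose; the values used above are examples only.

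The cost is one paragraph and a dated decision, with no extra patients or data. The downside is that the Steering Committee loses the Data Monitoring Committee's advice on this point.

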### Generalisability of the trial results

The results of this trial can be applied to similar patients in the future. It is, therefore, very important to describe in detail the characteristics of the patients randomised, as we will do. Inevitably, there will be some eligible patients who, for some reason, do not get randomised. However, our inclusion criteria are broad, and we envisage that across all centres, a very wide variety of patients will be randomised. We will collect the numbers of operated patients in each trial centre to gain some idea of the overall experience of the centre and what proportion of their patients enter the trial.

### Organisation

The Steering Committee will usually meet every six months to review the progress of the trial, including the overall complication rates of surgery. However, apart from the trial statistician, all the members of the committee will remain blinded to any outcomes and other important results divided by treatment allocation.

All members of the Data Monitoring Committee will be totally independent of the trial. The Data Monitoring Committee will regularly review the recruitment into the trial, trial discipline, the baseline data and the main outcomes. They will advise the Steering Committee on the adequacy of recruitment, the balance of the two treatment arms, and that there is no accumulating evidence of harm to one arm or the other. In this task they may request whatever unblinded analyses they wish from the trial statistician, and at whatever interval they wish. The Committee may also wish to consider any new information arising from other studies. All unblinded analyses are supplied to the Data Monitoring Committee in confidence.

The Data Monitoring Committee will advise the chairman of the Steering Committee if, in their view, the randomised comparisons have provided both: (i) 'proof beyond reasonable doubt' that for all, or some patients, one method of anaesthesia is clearly indicated or clearly contra-indicated; and (ii) evidence that might reasonably be expected to materially influence future patient management. Appropriate criteria of proof beyond reasonable doubt cannot be specified precisely, but we imagine the DMC will work to the well established guide that a difference of at least 3 standard errors in an interim analysis of the primary outcome events (between patients allocated local anaesthesia and patients allocated general anaesthesia) may be needed to justify halting or modifying the study before the planned completion of recruitment. This criterion has the practical advantage that the exact number of interim analyses is of little importance, and so no fixed schedule is proposed.
